## Abstract

Turner Syndrome (TS) is a sex chromosome aneuploidy (45,X) associated with social skill difficulties. Recent clinical care guidelines recommend that the Program for the Education and Enrichment of Relational Skills (PEERS) social skills intervention programme be trialled in this population. PEERS has been successfully used in adolescents with autism spectrum conditions without intellectual disabilities. The PEERS program will be piloted with adolescents and young women with TS aged 16-20 using an uncontrolled study trial with a multiple-case series design. The program will be delivered face to face and online. The assessment battery is designed to measure social skills comprehensively from diverse informants (parent, teacher young person). It includes measures of social performance, social knowledge and social cognition. Parents and young people taking part in the intervention will also feedback on the acceptability and feasibility of the pilot. The outcomes of this small scale pilot (n=6-10) will be used to adapt the programme based on feedback and estimate the sample for a future randomised controlled trial.

## Introduction

Turner Syndrome (45,X; TS) is one of the most common sex chromosome aneuploidies, with an incidence of 1 in 2500 female births
^1^. TS is associated with a variety of morbidities affecting nearly every bodily system, including skeletal abnormalities such as short stature, dysmorphic features, hearing difficulties, infertility, cardiac abnormalities, diabetes and thyroid problems. These difficulties have been well characterized in the literature (see Gravholt
*et al.* 2017
^2^ for the most recent review) and require clinical monitoring across the lifespan.

TS females have social difficulties throughout childhood, but these become more apparent in adolescence when socialisation becomes more complex
^3^. Social deficits are exemplified by difficulties integrating within social groups, with poor deciphering and processing of social cues
^3^. Previous research has shown TS is associated with specific deficits in social cognitive competence, especially forming and maintaining peer relationships
^4^.

Some of the social deficits observed in TS are reminiscent of difficulties associated with Autism Spectrum Disorders (ASD). Psychosocial evaluations of young women with TS have found an association with ASD
^5–
9^, anxiety disorders, depression and low self-esteem
^10–
13^.

Social skills deficits are known to have a significant impact on academic, adaptive and psychological functioning
^14–
17^, and are likely to have a substantial impact on the wellbeing of girls and women with TS across the lifespan
^3^. At present, psychosocial intervention research with young women with TS is scarce; only one intervention targeting self-esteem in adults aged 18–30 has been documented in the literature
^10^. The latest TS Clinical Care Guidelines recommend that a social skills training intervention should be trialled in this population
^2^. They suggest using the Program for the Education and Enrichment of Relational Skills (PEERS) developed for children with ASD
^18^. There is good evidence for the efficacy of PEERS when delivered with children and young adults with ASD without intellectual disabilities
^19–
24^. This pilot project will be the first to examine the feasibility and acceptability of the PEERS Protocol in adolescents with TS.

## Protocol

### Objectives and hypothesis

The main objectives of the study are:

1) To pilot the PEERS intervention in adolescents with TS;2) Assess its feasibility and acceptability to families.

We hypothesise social skills training will improve social competence with peers and may produce secondary improvements in social cognition, self-esteem and anxiety (social and generalised).

### Study design

We will be employing an uncontrolled trial design. To maximise the clinical reliability of the trial we will use a systematic multiple-case series design with case tracking. We aim to recruit participants with a similar degree of social impairment, and intellectual ability.

### Sample size

A sample size of 6–10 girls and their parents will be invited to take part in the study - this is the group size recommended by the PEERS intervention manual. At present the effect size for this intervention in girls with TS is unknown. This pilot will serve as the basis to estimate the intervention’s effect size and sample size for a future randomised control trial.

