### Statistical analysis

The primary outcome measure (SCP questionnaire)
^16^ will be analysed using visual analysis and multi-level modelling to track individual participant changes over 9 months from baseline to follow up
^39^.

The secondary outcome measures will be analysed for pre-post differences. Data will be analysed using SPSS version 22 statistical software. It is likely that we will be underpowered to detect any significant statistical differences between the pre and post intervention scores; therefore effect sizes (Cohen’s d) will also be calculated. The parent, teacher and adolescent responses to the questionnaires will also be compared to investigate the consistencies between different informants.

We anticipate that adolescent informants will report the greatest positive changes compared to other informants. We also anticipate that the adolescents will report greater improvements on the social knowledge on the TASSK, than on the social performance on the SCP or SDQ (prosocial or peer scale) and social cognition on the SASI. We also expect to see secondary improvements on adolescent self-reports of anxiety on the BAI raw score, social anxiety on the SWS raw total score and self-esteem on the RSE raw total score. We expect to see an increase in camouflaging on the CAT-Q on all the subscales.

In line with previous social skills intervention research we anticipate that positive changes in social performance will be noted by the parents, but that schoolteachers will not observe a change post intervention on the SRS, SDQ and SWS. Specifically we expect parents to report improvements in the SWS total raw score, as well as improvements on the SDQ raw prosocial scale and peer difficulties scale, and improvements on the SRS social communication scale and repetitive and ritualised behaviours scale.

The acceptability of the intervention to families will be assessed using the IAQ. Descriptive statistics will be used to summarise the responses alongside a qualitative summary of the open text answers. We expect that most families will report having positive experiences of the PEERS programme. Based on previous randomised controlled trials we predict that adherence will be on average 80% and that up to two participating families may dropout (Laugeson
*et al.,* 2015; Schohl
*et al.,* 2014).

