## Conclusion

This will be the first social skills training programme trialled with adolescents and young women with TS. Should the trial prove successful, the initial results will be used to inform the sample size for a future randomised controlled trial. Additionally, neither research trials using the PEERS program exclusively in girls, nor trials delivering PEERS online have been published. Therefore, this trial may have a broader impact on the development of treatment strategies for both for young women that experience social skills difficulties (including those on the autistic spectrum), but also for broadening access to treatment by using technology.

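### The article makes an uncontrolled pilot of 6–10 girls the basis for the effect size and sample size of a future RCT, which this design cannot supply

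*Protocol article*

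**What the plan says.** The Sample size section of the protocol article sets the number: "A sample size of 6–10 girls and their parents will be invited to take part in the study". The reason given is that "this is the group size recommended by the PEERS intervention manual"; no power or precision calculation lies behind it. The section adds: "At present the effect size for this intervention in girls with TS is unknown". It then makes the pilot the basis for estimating the intervention's "effect size and sample size for a future randomised control trial".

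The Abstract repeats the sample-size use, and so does the Conclusion: "Should the trial prove successful, the initial results will be used to inform the sample size for a future randomised controlled trial". Only the Sample size section speaks of an effect size for the RCT.

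Other sections bear on whether the design can do this:

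- Study design: the trial is uncontrolled.
- Assessments, Table 1: the parent SCP is collected every 4 weeks, nine times in all. Weeks 0, 4, 8 and 12 come before treatment.
- Statistical analysis: the SCP gets visual analysis and multi-level modelling. Secondary outcomes get pre-post comparisons, with Cohen's d added because "It is likely that we will be underpowered to detect any significant statistical differences between the pre and post intervention scores". The authors also expect that "up to two participating families may dropout".
- Discussion: parent and adolescent reports are expected to be prone to expectancy bias and may exaggerate treatment effects.

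**The concern.** An RCT is sized on the difference between treatment and control. One treated group gives change from before to after. That change also contains whatever would have happened anyway: maturation, repeat testing, regression to the mean in girls selected for marked social difficulties, and informants' expectations. Nothing in this design separates these parts fully.

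Even without that bias, 6–10 girls fix a standardised effect very loosely. With up to two families lost, the evaluable number is anywhere from 4 to 10.

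The planning of the next trial is at stake. An estimate that is too large gives an RCT with little chance of detecting a real benefit in a rare condition. One that is too small by chance could lead to a useful programme being dropped or to an unachievable recruitment target.

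**Working it through.** **The plan's own figure.** The range 6–10 is a group size from the manual. It has no alpha, power, effect size or SD behind it, so there is nothing to reproduce. What follows shows what such a pilot could tell an RCT planner.

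**Inputs from the article.** n = 6 to 10; up to two families lost, so 4 to 10 evaluable; no control arm.

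**Assumptions not in the article.** RCT with 1:1 allocation, two-sided 5% test and 80% power; observed effect of 0.5 for illustration; pre-post correlation 0.3 to 0.8; change in controls of 0 or 0.2 SD.

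**Step 1: precision.** Let d be the mean change divided by the SD of change. Then t = d√n follows a noncentral t distribution with n − 1 degrees of freedom. The 95% limits are the noncentrality values that place the observed t at the 2.5% tail on either side, divided by √n. For an observed d of 0.5:

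| Evaluable n | 95% CI |
|---|---|
| 4 | −0.58 to 1.52 |
| 6 | −0.38 to 1.33 |
| 8 | −0.25 to 1.22 |
| 10 | −0.17 to 1.15 |

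Every interval includes zero and a very large effect.

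**Step 2: what that means for RCT size.** The normal approximation is n per arm = 2(1.960 + 0.842)²/d² = 15.70/d². The exact two-sample t calculation adds about one per arm.

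- d = 0.5: 15.70/0.25 = 62.8, so 63 by the approximation and 64 by the t calculation.
- d = 1.15 (upper limit at n = 10): 15.70/1.3225 = 11.9, so 12, or 13 by the t calculation.
- d = −0.17 (lower limit at n = 10): no finite size.

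This step treats the change-score d as a between-arm d. The two are related by d(change) = d(raw)/√(2(1 − r)), where r is the pre-post correlation, and they agree only at r = 0.5. A change of 0.5 raw SDs becomes 0.42, 0.50, 0.65 or 0.79 for r = 0.3, 0.5, 0.7 or 0.8. The choice of standardiser therefore adds to the uncertainty.

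**Step 3: bias from having no control arm.** Suppose 0.2 of an observed 0.5 would also occur in controls. The between-arm effect is then 0.5 − 0.2 = 0.3. The RCT needs 15.70/0.09 = 174.4, so 175 by the approximation and 176 by the t calculation. An RCT of 63 or 64 per arm, planned on 0.5, has 39% power.

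**Step 4: how often the pilot would size the RCT well.** This was simulated with 20,000 pilots per n, a true between-arm d of 0.5, r = 0.5 and the average of the pre and post SDs as standardiser. Pilots with no usable positive d were set aside. Shares for n = 6 to 10, with a dash where no figure is used here:

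| True power of the resulting RCT | No change in controls | Controls also improve by 0.2 |
|---|---|---|
| Below 60% | 36–40% | 58–59% |
| 70–90% | 12–16% | – |
| Above 95% | 27–29% | – |

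**The case against.** The strongest reply is that the primary outcome is not a bare pre-post comparison. Four parent SCP scores precede treatment, so the multi-level model can allow in part for a prior trend and for repeat testing. That stands, and it makes the SCP estimate better than a simple difference. It does not supply a control arm, remove expectancy bias in the parents who give the scores, or cure the small n.

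A second reply is that the main objectives are feasibility and acceptability, and that the Abstract and Conclusion speak only of informing the sample size. That also stands. A pilot SD, correlation and dropout rate can properly do this. The difficulty is the Sample size section, which claims the effect size as well.

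Some stronger readings are tempting but not supported:

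- A reader might infer that the RCT will be sized on the pre-post Cohen's d. It is the only effect size named, but it appears with the secondary outcomes and no section links it to the RCT.
- A reader might take evaluable n to be 4–8. That assumes both families are always lost; the text allows for none, one or two.
- A reader might infer selection on a significant result from the Conclusion's condition that the trial prove successful. Success is not defined there, and the authors expect the tests to be underpowered.
- A reader might argue that recruiting similar girls ("We aim to recruit participants with a similar degree of social impairment, and intellectual ability") shrinks the SD and inflates d. Similar impairment and ability at entry need not narrow the SD of change, and a future RCT might recruit similarly.
- The absence of small-sample corrections or intervals for d is a detail commonly left to a full protocol or SAP. It is not part of this point.

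**Conclusion.** The point holds for the claim in the Sample size section. That section gives the pilot a use that an uncontrolled group of 6–10 cannot serve, whichever outcome or model supplies the estimate. The result would be biased by an unknown amount and too imprecise to choose between an RCT of about a dozen per arm and one with no finite size.

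The RCT is likely, not certain, to be mis-sized: in the simulation a minority of pilots still landed near the intended power. The lack of a between-arm estimate follows from the design alone. The numbers rest on the assumed alpha, power, allocation, illustrative effect, correlation and control-group change.

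This should be fixed, but it is not critical. It affects the planning of a later trial and leaves the conduct, data and two main objectives of this pilot untouched.

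**What to change.** In the Sample size section, delete the claim that the pilot will estimate the intervention's effect size for the RCT. State there, and consistently in the Abstract and Conclusion, that:

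- the pilot will inform RCT planning through retention, adherence, data completeness, and the SCP standard deviation and within-person correlation, each with its uncertainty;
- the RCT target difference will come from a minimum important difference or from controlled PEERS trials;
- any effect size from the pilot is descriptive, reported with a 95% confidence interval, and not used to size the RCT.

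One way to carry the SD's uncertainty forward is to plan on its upper one-sided 80% limit, SD × √((n − 1)/χ²), where χ² is the 20th percentile on n − 1 degrees of freedom. At n = 8 this is √(7/3.82) = 1.35 times the observed SD.

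The cost is wording only. No assessment, visit or participant is added; the stated aim becomes more modest.

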### Study centres/Recruitment

Participants will be recruited from the
*Social Skills and Relationships in Turner Syndrome Study* (SOAR), which recruits children and young women with TS from the Turner Syndrome Support Society, the NHS Great Ormond Street Hospital and the NHS University College London Hospitals. 

The SOAR study is conducting online mental health and social cognition questionnaires with 200 girls and young women with TS and their parents. A subset of families from this large cohort that meet the trial’s inclusion criteria will be invited to take part in the intervention study.

### Participant inclusion and exclusion criteria

Inclusion criteria for the intervention include: 1, a confirmed diagnosis of TS (monosomy, variant, mosaic etc.); 2, age 16–20 years; 3, significant social skills difficulties as screened for in the SOAR online questionnaires (see screening assessment measures section for details) and clinical judgement; 4, motivation to take part.

The exclusion criteria for the intervention include: 1, profound hearing or vision impairments (eg. complete deafness or blindness); 2, intellectual disability (VIQ<70); 3, concurrent participation in other psychological treatment.

### Intervention

The UCLA PEERS for Adolescents is a manualized treatment program that consists of 14 90 min sessions
^18^. The program runs two concurrent groups, one for the adolescents and one for parents. At the end of each session the two groups are reunited for review and questions. Between sessions the adolescent group are given homework tasks, which they are to complete with the help of their parent who is trained to support them as their social coach. Parents are provided with concise handouts for each session, which include an overview of the lesson material and the homework.

The adolescent group sessions are structured to provide didactic instruction as well as social skill rehearsal. The parent sessions mirror the adolescent sessions and provide a space for the parents to problem-solve any difficulties they may have encountered the previous week. The didactic lessons provide instruction on (a) conversational skills; (b) electronic forms of communication; (c) developing friendship networks and finding sources of friends; (d) appropriate use of humour; (e) peer entry strategies; (f) peer exit strategies; (g) organizing get-togethers with friends; (h) handling teasing and embarrassing feedback; and (i) resolving arguments with friends
^18^.

The adolescents and parents will attend separate concurrent sessions led by a certified PEERS Instructor. Three face to face sessions will take place in London at the start, middle and end of the program. All other sessions will be conducted online using a virtual meeting room. The face to face sessions will deliver two PEERS lessons, whereas the weekly online sessions will deliver one lesson. Research assistants (graduate or undergraduate psychology students) will monitor treatment fidelity, assist with role-playing demonstrations, and provide social coaching with performance feedback during behavioural rehearsal exercises. All research assistants will be trained and supervised throughout the intervention.

### Assessments

Participants will complete assessments at different time points throughout the study. The study will last 9 months in total, including a 3 month baseline, 2 months of intervention and a 3 month follow-up period. The screening measures will be delivered at T=0, the baseline assessments will be delivered at T=12 weeks and the post intervention assessments will be delivered at T=20 weeks. The primary outcome measure will be delivered at regular intervals of 4 weeks throughout the course of the study (see
Table 1).

**Table 1. T1:** Assessment timeline. Informants for each assessment are included in brackets (P – Parent; T – Teacher; YP – Young Person). Assessment acronyms: BAI – Beck’s Anxiety Inventory; IAQ – Intervention Acceptability Questionnaire; PEERS – Program for Education and Enrichment of Relational Skills; PEERS QSQ – PEERS Quality of Socialisation Questionnaire; PEERS TASSK – PEERS Test of Adolescent Social Skills Knowledge; RSE – Rosenberg Self-esteem Scale; SCP – Social Competence with Peers; SDQ – Strengths and Difficulties Questionnaire; SRS – Social Responsiveness Scale; SASI - Schedules for the Assessment of Social Intelligence; SWS – Spence Social Worries Scale; WAIS-Wechsler Adult Intelligence Scale.

Timeline	Assessments
t=0	SCP (P) 1 PEERS Screener (P,YP) SASI (YP) WAIS (YP)
4 weeks	SCP (P) 2
8 weeks	SCP (P) 3
**Baseline** 12 weeks	SCP (P,YP,T) 4 SWS (P,YP,T) PEERS QSQ (P) PEERS TASSK (YP) RSE (YP) BAI (YP) SRS (P,T) SDQ (P,T)
16 weeks	SCP (P) 5
**Post-intervention** 20 weeks	SCP (P) 6 SWS (P,YP,T) PEERS QSQ (P) PEERS TASSK (YP) RSE (YP) BAI (YP) SRS (P,T) SDQ (P,YP,T) IAQ (P,YP) SASI (YP)
24 weeks	SCP (P) 7
28 weeks	SCP (P) 8
**Follow-up** 32 weeks	SCP (P,YP,T) 9

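### BAI, SWS and RSE are first measured at week 12, so the untreated lead-in gives no estimate of untreated change on scales that carry stated secondary hypotheses

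*Protocol article*

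**What the plan says.** Under Study design the protocol states: "We will be employing an uncontrolled trial design". Under Assessments it sets out the phases, "including a 3 month baseline, 2 months of intervention and a 3 month follow-up period", and the timing: "the baseline assessments will be delivered at T=12 weeks and the post intervention assessments will be delivered at T=20 weeks".

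In Table 1 the t=0 row reads "SCP (P) 1 PEERS Screener (P,YP) SASI (YP) WAIS (YP"). Weeks 4 and 8 contain parent SCP only. The week 12 row contains "SWS (P,YP,T) PEERS QSQ (P) PEERS TASSK (YP) RSE (YP) BAI (YP"), and the same run of entries returns at week 20. BAI, SWS and RSE appear in no other row. The section on secondary outcome measures agrees: each of the three is given at baseline and post-intervention. None of them is in the list of screening assessments.

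Only the primary outcome is spread across the lead-in: "The primary outcome measure will be delivered at regular intervals of 4 weeks throughout the course of the study".

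Under Objectives and hypothesis, the intervention "may produce secondary improvements in social cognition, self-esteem and anxiety (social and generalised"). Under Statistical analysis, "We also expect to see secondary improvements on adolescent self-reports of anxiety on the BAI raw score", and the same sentence extends this to SWS for social anxiety and RSE for self-esteem. Parents are also predicted to report improvement on SWS. Secondary outcomes are to be analysed as pre-post differences, with Cohen's d added because low power is expected.

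**The concern.** Without a parallel group, the period before treatment is the only place where untreated change can be seen. The protocol uses it for parent SCP but not for three scales on which it predicts improvement. Their first completion falls just before the group begins and their second as it ends. Three things unrelated to PEERS could move the score between those points: natural drift over time, a shift between a first and a second completion of the same questionnaire, and worry that is temporarily high at week 12 because a new group is about to start. All three would enter the pre-post d.

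This matters here because the protocol expects significance tests to be uninformative and turns to effect sizes. A bias in d is not reflected in its confidence interval. A later analysis plan cannot repair the gap either, because the t=0 scores would never have been collected.

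**Working it through.** The plan gives no calculated figure on this point, so there is none to reproduce.

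**Step 1. Count the untreated measurements (weeks 0 to 12, from Table 1).** An untreated change needs at least two.

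| Scale | Weeks measured | At or before week 12 | Untreated change estimable? |
|---|---|---|---|
| SCP (parent) | 0, 4, 8, 12, 16, 20, 24, 28, 32 | 4 | yes |
| BAI | 12, 20 | 1 | no |
| SWS | 12, 20 | 1 | no |
| RSE | 12, 20 | 1 | no |

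QSQ and TASSK are also first taken at week 12. The point is made for BAI, SWS and RSE because the hypotheses on anxiety, social anxiety and self-esteem rest on them.

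**Step 2. How large could the bias be?** The documents give neither a retest correlation nor an untreated shift, so both are assumptions: correlation ρ of 0.6 to 0.8, shift of 0.2 to 0.3 baseline SD, equal SDs at each time, and no treatment effect.

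SD of change = √(2(1 − ρ)); d = shift / SD of change.

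| ρ | SD of change | d, shift 0.2 | d, shift 0.3 |
|---|---|---|---|
| 0.6 | 0.89 | 0.22 | 0.34 |
| 0.7 | 0.77 | 0.26 | 0.39 |
| 0.8 | 0.63 | 0.32 | 0.47 |

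The protocol does not name the standardiser for Cohen's d. If d is scaled by the baseline SD, the same shifts give simply 0.2 to 0.3.

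**Step 3. Compare with sampling error.** In change-SD units the SE of a mean change is about 1/√n: 1/√10 = 0.32 and 1/√6 = 0.41. The assumed bias is of the same order.

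**Step 4. What would a t=0 score allow?** Each scale would have a week 0-12 change and a week 12-20 change. Scaling the first to 8 weeks (8/12 = 2/3) gives the contrast

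(y20 − y12) − (2/3)(y12 − y0) = y20 − (5/3)y12 + (2/3)y0.

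With the same correlation between all pairs of times, its variance is (1 − ρ)(1 + 25/9 + 4/9) = 4.22(1 − ρ), against 2(1 − ρ) for the simple change. The SE ratio is √(4.22/2) = 1.45. The contrast SE is therefore 1.45 × 0.32 = 0.46 (n = 10) to 1.45 × 0.41 = 0.59 (n = 6), and the 95% half-width is 2.26 × 0.46 = 1.0 to 2.57 × 0.59 = 1.5.

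The week 12 score has weight 5/3 in this contrast, and weight 2 if the two changes are subtracted unscaled, against 1 in the simple pre-post change. A temporary rise at week 12 is therefore magnified by the contrast: 5/3 is 67% more than 1.

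**The case against.** The schedule contradicts nothing. The protocol calls the trial uncontrolled, gives repeated measurement to the primary outcome only, and matches its analysis to that. Its main objectives are piloting, feasibility and acceptability; the secondary hypothesis is worded cautiously; low power and expectancy bias are conceded; and a randomised trial is to follow. All of this stands, and it makes the point a missed use of the lead-in rather than an error.

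The SDQ, which has an emotional-symptoms scale, is listed among the screening measures, and those are placed at T=0. This could give a related untreated comparison. It is, however, a different instrument from those named in the hypotheses, and the t=0 row of Table 1 omits it.

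The size of the bias is hypothetical: no passage supplies the shifts or the correlation, and the upper value of 0.47 depends on scaling by the change SD. That also stands, and the figures are offered only as an illustration.

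The strongest objection concerns what a t=0 score could achieve. A reader might infer that, once it exists, improvement can be credited to PEERS wherever the treated change exceeds the untreated one. The design does not support that. With no drift and no effect, and symmetric errors, the condition is met about half the time. A temporary week 12 rise, one of the very biases at issue, inflates the contrast. Scaling 12 weeks to 8 assumes linear drift, which does not describe a shift between first and second completion. And the assumed bias is at or below about one SE of the contrast.

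**Conclusion.** The point holds as a cheap improvement. As scheduled, untreated change on BAI, SWS and RSE cannot be estimated, so an improvement between weeks 12 and 20 cannot be told apart from change that would have occurred without PEERS. This follows from Table 1 alone and needs no assumption. The possible size (d of 0.22 to 0.47 on the change-SD scale, 0.2 to 0.3 on the baseline-SD scale) rests wholly on the assumed shift and retest correlation.

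Two stronger conclusions should not be drawn. Nothing in the documents shows that such a shift will occur, so a future improvement on these scales should not be presumed an artefact. Nor would a t=0 score turn this pilot into a test of the effect on them: with 6 to 10 girls it would display the untreated change, imprecisely, and could not decide attribution.

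**What to change.** Add BAI (young person), RSE (young person) and SWS (parent and young person) to the t=0 row of Table 1, and align the text on secondary outcome measures. Report the week 0-12 and week 12-20 changes side by side, for each girl and for the group, with intervals and as description only. Do not adopt a rule that attributes improvement to PEERS when the treated change is the larger. State instead that change on these scales cannot be attributed to PEERS from this pilot alone. If the schedule is left as it is, that statement is still needed.

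The cost is an amendment to Table 1 and four extra questionnaire completions per family at t=0 (BAI, RSE and two SWS forms). Girls and parents already complete assessments at t=0, and the protocol has these scales completed online, so no new visit is needed. The documents do not give the length of the scales, so the added burden cannot be stated in minutes. The other downside is that the untreated estimate will be imprecise.
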